### Statistical analysis

Primary outcomes will be analysed with standard methods for a binary outcome. Risk difference and odds ratio between two groups and their 95% confidence intervals for AAD and CDAD will be estimated. In addition, covariate adjustment analysis that includes the relevant covariates (such as age, gender, specific antibiotic, centre) will be performed. To explore whether prevention strategies should be provided to all patients or just those at high risk of diarrhoea, we will assess probiotic efficacy according to known or potential risk factors for AAD and CDAD as described previously. Sub-group effects will be identified by inspection of interaction terms, and these will be interpreted in light of power relative to main effects and supporting evidence of mechanism [31]. All analyses will be performed using SAS PROC PLAN Version 9.1 (SAS Institute Inc., Cary, NC, USA).

There are few tools that are validated for measuring QoL in older people and none specifically targeted at treatment-induced diarrhoea. We will use the generic measures EQ-5D and the York SF12 [32] to understand the broader health impact related to treatment-induced diarrhoea and facilitate cost-effectiveness analysis.

Health economic analysis will be undertaken from the perspective of the UK NHS. Resources utilised by each participant will include the cost of the probiotics, staff time involved in administering probiotics, treatment of adverse events, assessment of cases of diarrhoea (stool collection and culture/toxin assay, endoscopy) and the costs of dealing with and treating diarrhoea such as laundry, antibiotics, increased hospital stay and co-morbidities. Unit costs will be determined from discussion with relevant clinicians and finance department staff as well as from recognised published information.

Cost differences between the probiotic and placebo group will be determined and used in conjunction with differences in outcomes between groups in undertaking a cost-consequences analysis. Cost per case of diarrhoea averted will be the primary outcome measure. Sub-group analyses will determine the relative cost-effectiveness of preventative strategies in different risk groups. In addition, a cost-utility analysis will be undertaken based on the differences in costs between the two groups and in quality-adjusted life years derived from responses to the EQ-5D questionnaire.

Given the short timescale of the project, there will be no discounting of the costs or benefits. Sensitivity analyses will investigate the robustness of the results to changes in estimated costs and outcomes and probabilistic sensitivity analysis will use bootstrap resampling to determine the probability that preventive strategies are within certain thresholds. The budgetary impact from a UK NHS perspective of adopting a policy of administering a probiotic preparation to prevent or ameliorate AAD and CDAD in people aged 65 years and over admitted to secondary care NHS facilities and receiving oral or intravenous antibiotics will also be assessed.

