### Generation and concealment of a random allocation sequence

A random allocation sequence using blocks of variable sizes will be produced using SAS PROC PLAN Version 9.1 (SAS Institute Inc., Cary, NC, USA). The sequence will allocate participants to either placebo or probiotic on a 1:1 basis and be stratified by centre to ensure that similar numbers of patients will be allocated to each arm of the study in each centre. The allocation sequence will not be available to members of the research team during participant recruitment and follow-up.

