### Outcome measures

The two outcomes used to generate the sample size, AAD and CDAD, have been identified as co-primary outcomes (Table 3). Diarrhoea is defined as 3 or more loose stools in a 24 h period. We will use the Bristol Stool Form Scale [29] to assist participants in describing stool consistency; types 5-7 will be consistent with diarrhoea.

**Table 3 T3:** Outcome measures

**Primary outcomes**	1. the occurrence of AAD
	2. the occurrence of CDAD
	1. severity^1^ and duration of AAD
	2. severity^1,2^ and duration of CDAD and incidence of recurrence within the 8-12 weeks follow-up period
	3. abdominal symptoms (abdominal pain, bloating, flatus, nausea)
**Secondary outcomes**	4. well-being and quality of life assessed using the generic measures EQ-5D and the York SF12 (Iglesias 2001) at recruitment and 4 and 8 weeks
	5. duration of hospital stay
	6. serious adverse effects
	7. acceptability of the probiotic preparation
	8. viability of the probiotic at point of administration
	9. cost-effectiveness

^1^Frequency and consistency of stools. ^2^Additional information extracted from the clinical records (*e.g.* laboratory parameters, findings at sigmoidoscopy, pseudomembraneous colitis, colectomy, death).

All participants who develop diarrhoea during the study period will be asked to provide a stool sample and this will be collected during a home visit if required. The cause of diarrhoea will be determined by NHS laboratories according to their usual practice. Stools will be analysed for diarrhoeal pathogens (bacterial culture for *Salmonella* sp, *Shigella* sp, Campylobacter, *E. Coli* 0157; wet film for ova, cysts and parasites) and for *C. difficile* toxins. In ABMUHB, *C. difficile* will be identified by an in-house culture assay with further analysis by Meridian Premier Toxin A + B Enzyme Immunoassay (Meridian Bioscience Europe Inc., Cincinnati, USA) if required. In CDDFT, toxins are identified using the mini VIDAS system (C. diff Quik Check, Techlab, Blacksburg, U.S.A.). If a cause of the diarrhoea is not identified, a further stool sample will be collected and tested 2 days later.

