### Sample size and recruitment

Conservatively, we expected ADD to occur in 20% and CDAD in 4% of participants allocated to the placebo group [2]. To detect a 50% reduction in the frequency CDAD in the probiotic group (i.e. 2% frequency) with 80% power at the 5% significance level, would require 2,478 subjects (1,239 in each group; 1:1 allocation). At the 5% significance level, this number of participants would provide a power of ≫99% to detect a 50% reduction in ADD (i.e. 10% frequency) and a power of 90% to detect a 25% reduction in ADD (i.e. 15% frequency) in the probiotic group. To allow for 10% drop-outs and 10% loss to follow-up due to deaths unrelated to diarrhoea, we plan to recruit 2,974 participants.

Based on data from 2005/6, about 14,000 patients per year aged ≥65 years and exposed to antibiotics were admitted to the study hospitals and there was a total of 963 cases of CDAD. Conservatively, we expect to be able to recruit between 1:9 and 1:10 of eligible patients (approximately 124 patients/month) and undertake recruitment for a total of 24 months. This estimate was supported by a 2-week pilot study of the recruitment process in 23 medical and surgical wards in Morriston Hospital when research nurses visited the wards daily. Out of a total of 253 admissions aged ≥65 years, 166 patients were excluded (152 patients had no current or planned exposure to antibiotics; 12 already had diarrhoea [including 1 CDAD]; 1 active inflammatory bowel disease; 1 reported a previous adverse reaction to a probiotic). Eighty-seven (34.4%) patients were eligible to participate in the pilot study but 8 of these were either confused or not available (in theatre or undergoing investigations). Therefore, the study design was explained to 79 patients (31.2% of total admissions) and 58 (73.4%) stated that they would have agreed to participate in this study.

We will monitor the number of participants reaching study endpoints in each hospital every 3 months. The ethical permission secured for the study included all hospitals within each health authority providing an ability to extend recruitment if needed.

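### Allocation is stratified by centre, but the main analysis appears to leave centre out: a small, avoidable loss of efficiency

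*Protocol article*

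**What the plan says.** Under Generation and concealment of a random allocation sequence, the article states "A random allocation sequence using blocks of variable sizes will be produced", with 1:1 allocation. The sequence is to "be stratified by centre to ensure that similar numbers of patients will be allocated to each arm of the study in each centre". Centre is the only stratification factor. Whether it means the two health regions or the five hospitals is not stated.

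Under Statistical analysis, the main analysis is given in two sentences: "Primary outcomes will be analysed with standard methods for a binary outcome" and "Risk difference and odds ratio between two groups and their 95% confidence intervals for AAD and CDAD will be estimated". The next sentence is the only place where the analysis text names centre: "In addition, covariate adjustment analysis that includes the relevant covariates (such as age, gender, specific antibiotic, centre) will be performed".

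Two sections give reasons why rates may differ by centre. Under Outcome measures, "The cause of diarrhoea will be determined by NHS laboratories according to their usual practice", and the two regions use different *C. difficile* tests: an in-house culture assay with immunoassay if required in South West Wales, and a mini VIDAS toxin system in County Durham and Darlington. Under Investigational medicinal products, capsule taking in hospital is supervised by research nurses in the first region and by ward nurses in the second.

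**The concern.** Blocking within centre forces the arms to be balanced on centre. If centre is related to outcome, that balance makes the treatment difference less variable than a simple two-sample formula assumes. An analysis without centre therefore reports standard errors that are too large and gives away part of what the stratification gained.

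A relation between centre and outcome is plausible here. AAD requires a negative toxin result and CDAD a positive one, so a difference in test sensitivity between regions can move cases from one co-primary outcome to the other. A difference in supervision could change adherence, and so the event rate in the probiotic arm.

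At stake are precision and a little power, not validity.

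**Working it through.** **The plan's own figure.** Inputs from Sample size and recruitment: "we expected ADD to occur in 20% and CDAD in 4% of participants allocated to the placebo group", a 50% reduction in CDAD, 80% power, 5% significance, 1:1 allocation. The two-proportion formula with continuity correction, two-sided, gives 1,239 per arm, 2,478 in total, which is the stated number. It is an unstratified calculation. At 1,239 per arm, power for AAD 20% vs 15% is 90.6% (89.7% with continuity correction), against the stated 90%. The powers below use no continuity correction, so CDAD starts from 83.1% rather than 80%.

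**Effect of leaving centre out.** Take equal-sized centres with 1:1 balance in each, centre rates p_c with mean P and variance V, and n = 1,239 per arm. With no treatment effect:

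- variance used by the unadjusted test: 2P(1−P)/n
- true variance: 2[P(1−P) − V]/n
- share of variance between centres: s = V/[P(1−P)]
- excess width of the interval: 1/√(1−s) − 1
- true type I error: 2[1 − Φ(1.96/√(1−s))]

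Power comes from the matching normal approximation, with the same proportional reduction in every centre (25% for AAD, 50% for CDAD). The centre rates are assumptions.

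| Assumed placebo rates | s | Interval too wide by | Type I error, unadjusted | Power, unadjusted | Power, stratified | Gap (points) |
|---|---|---|---|---|---|---|
| AAD 20% everywhere | 0 | 0 | 5.0% | 90.63% | 90.63% | 0 |
| AAD 10, 15, 20, 25, 30% (five centres) | 0.005/0.16 = 3.1% | 1.6% | 4.64% | 90.93% | 91.36% | 0.43 |
| AAD 10%, 30% (two centres) | 0.01/0.16 = 6.3% | 3.3% | 4.29% | 91.24% | 92.07% | 0.83 |
| AAD 5%, 35% (two centres, extreme) | 0.0225/0.16 = 14.1% | 7.9% | 3.45% | 92.03% | 93.77% | 1.74 |
| CDAD 2, 3, 4, 5, 6% (five centres) | 0.0002/0.0384 = 0.5% | 0.3% | 4.94% | 83.19% | 83.29% | 0.10 |
| CDAD 2%, 6% (two centres) | 0.0004/0.0384 = 1.0% | 0.5% | 4.88% | 83.25% | 83.44% | 0.19 |
| CDAD 1%, 7% (two centres) | 0.0009/0.0384 = 2.3% | 1.2% | 4.73% | 83.38% | 83.81% | 0.43 |

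The stratified test stays at 5.0% throughout.

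**Simulation check.** With 100,000 trials per scenario, type I error of the unadjusted test was 4.71% (AAD, five centres), 4.22% (AAD 10%/30%), 4.94% (CDAD, five centres) and 4.76% (CDAD 1%/7%). The Cochran-Mantel-Haenszel test gave 4.95% to 5.07%. Power gaps were 0.40, 0.84, 0.01 and 0.24 points.

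**What the test difference alone could do.** Suppose one region's test missed half of a 4% CDAD rate (assumption) and those cases were counted as AAD. AAD would be 20% in one region and 22% in the other: V = 0.0001 and s = 0.0001/(0.21 × 0.79) = 0.06%. CDAD would be 4% and 2%: s = 0.0001/(0.03 × 0.97) = 0.34%. Both are near the bottom of the range above.

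**Odds ratio.** The unadjusted odds ratio is marginal and lies slightly nearer 1 than the centre-conditional one. For AAD 10%/30% reduced by 25% to 7.5%/22.5%, the unadjusted value is (0.15/0.85)/(0.20/0.80) = 0.706. The Mantel-Haenszel value is (0.075×0.9 + 0.225×0.7)/(0.1×0.925 + 0.3×0.775) = 0.225/0.325 = 0.692.

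**The case against.** The strongest reply has three parts.

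- **The wording does not say unadjusted.** A Mantel-Haenszel estimate is itself a standard binary method, and an analysis plan that is not shown may specify one. This stands in part: the main analysis being unadjusted is an inference. But the adjusted analysis is introduced as an addition to the two-group estimates, with centre as one example in it, so the inference is the natural one. The article states where centre goes; it does not leave that open.
- **The effect is tiny and in the safe direction.** This stands. The sample size calculation is also unstratified, so an unadjusted test matches the plan's own sizing.
- **The wide AAD spreads have no source.** This stands too. The documented differences in testing and supervision lie between two regions, not among five hospitals, and the test difference alone would move AAD very little.

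A reader might also infer that having an unadjusted and an adjusted result leaves it open which one is confirmatory. The wording does not support that: it ranks the adjusted analysis as additional. The open list of further covariates is detail that an article may leave to the analysis plan.

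**Conclusion.** The point holds as a minor mismatch between design and analysis. On the plain reading, the sole stratification factor is absent from the main estimates. Under the assumed spreads, leaving out the extreme one, the type I error is about 4.3% to 4.9% and the power loss is under 1 point (0.1 to 0.4 for CDAD by the normal approximation, no more in simulation). Even the extreme AAD spread costs only about 1.7 points. If rates do not differ by centre, nothing is lost.

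A reader might conclude that the main test is invalid or the trial too small. Neither follows: the risk difference is unbiased, the error rate is at or below nominal, and 2,478 stands. Nor is centre ignored altogether, since it is named in the additional analysis.

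The size rests on assumed centre rates, equal centres, close balance within centre and a constant proportional effect.

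**What to change.** Make the centre-stratified analysis primary for both AAD and CDAD: Mantel-Haenszel risk difference and odds ratio with 95% confidence intervals, and the Cochran-Mantel-Haenszel test. Stratify by the centre used in randomisation and state whether that is the two regions or the five hospitals. Keep the unadjusted estimates as supportive. Note that the primary odds ratio then becomes centre-conditional.

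The method suits the sparse outcome. About 1,239 × 0.04 = 50 and 1,239 × 0.02 = 25 CDAD events are expected, or roughly 10 and 5 per hospital if spread evenly over five, and Mantel-Haenszel methods cope with strata of that size.

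The cost is wording in the analysis plan. Sample size, data collection and conduct do not change.

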### Trial organisation and safety monitoring

The funders (the National Institute of Health Research Health Technology Assessment [HTA] Programme) will appoint the chairs and members for a Trial Steering Committee (TSC) and an independent Data Monitoring and Ethics Committee (DMEC). The DMEC will include an independent statistician who will generate and hold the random allocation sequence for the trial. Trial management will be centered in the Clinical Research Unit, Morriston Hospital, Swansea. A Trial Management Committee will include the Principle Investigator, the Project Manager, the CDDFT Site Co-ordinator and CDDFT hospital site leads.

In view of the expected high frequency of adverse events in an elderly population of hospital in-patients, the recording of gastro-intestinal symptoms during follow-up and the excellent safety record of probiotics, only information regarding serious adverse events (SAEs) will be recorded. SAEs will be defined and reported according to GCP guidelines [27], assessed by the local research clinicians involved in the project as to their attribution and reviewed regularly by an Independent Safety Monitor.

Suspected Unexpected Serious Adverse Reactions (SUSARs) will be defined as the development of:

1. bacterial infection (any manifestation of infection: abscess, bacterial endocarditis, bacteraemia etc.) where a lactobacillus or bifidobacteria is isolated in pathological specimens

2. multi-organ failure

3. bowel ischaemia

4. pancreatitis (abdominal pain with serum amylase or lipase concentration ≥3 times the institutional upper limit of normal)

SUSARs will be reported immediately to the Independent Safety Monitor to consider their attribution to the participant’s inclusion in the trial. It was considered that knowledge of a participant’s allocation would not inform the clinical management of an SAE or SUSAR and, therefore, procedures for the immediate unmasking of participant allocation will not be established. If required, unmasking could be undertaken by the Independent Statistician. The Independent Statistician will undertake an unblinded, interim analysis of SAEs and SUSARs in the first 500 participants with complete data and report the findings to the DMEC.

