## Abbreviations

AAD = Antibiotic associated diarrhoea; ABMUHB = Abertawe Bro Morgannwg University Health Board; B. bifidum = Bifidobacterium bifidum; B. lactis = Bifidobacterium lactis; CDAD = Clostridium difficile associated diarrhoea; CDDFT = County Durham and Darlington NHS Foundation Trust; DMEC = Data Monitoring and Ethics Committee; GCP = Good Clinical Practice; HTA = Health Technology Assessment; ICH = International Conference on Harmonisation; IMP = Investigational medicinal product; L. acidophilus = Lactobacillus acidophilus; MHRA = Medicines and Healthcare products Regulatory Agency; NCIMB = National Collection of Industrial, Food and Marine Bacteria; NHS = National Health Service; PLACIDE = Probiotic lactobacilli and bifidobacteria in antibiotic-associated diarrhoea and Clostridium difficile diarrhoea in the elderly; S. boulardii = Saccharomyces boulardii; SAE = Severe adverse event; SUSAR = Suspected unexpected serious adverse reaction; TSC = Trial Steering Committee.

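### SUSARs are defined by a closed list of four diagnoses instead of by suspected causality and unexpectedness, so the category omits unlisted related, unexpected SAEs and includes three diagnoses whatever their cause

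*Protocol article*

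**What the plan says.** All the relevant text is in the protocol article, Trial organisation and safety monitoring.

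- **Definition.** "Suspected Unexpected Serious Adverse Reactions (SUSARs) will be defined as the development of" is followed by four numbered items: a bacterial infection "where a lactobacillus or bifidobacteria is isolated in pathological specimens"; "multi-organ failure"; "bowel ischaemia"; and "pancreatitis (abdominal pain with serum amylase or lipase concentration ≥3 times the institutional upper limit of normal").
- **Route for SUSARs.** "SUSARs will be reported immediately to the Independent Safety Monitor to consider their attribution" to trial participation.
- **Route for all serious events.** "SAEs will be defined and reported according to GCP guidelines". Local research clinicians then judge attribution, and the Independent Safety Monitor looks at the events at regular intervals. No reporting time is given.
- **Interim look.** The Independent Statistician compares SAEs and SUSARs unblinded in the first 500 participants with complete data and reports to the DMEC.

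**The concern.** The acronym has content: the event must be serious, there must be suspicion that the product caused it, and it must be unexpected. The article spells the term out in full and then replaces that content with a list of diagnoses. Two errors of classification follow. A serious event that fits the term but is not on the list falls outside the category. An event on the list with an evident other cause falls inside it.

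At stake are the only route to the Independent Safety Monitor that the article describes as immediate, and the meaning of the SUSAR figure that the DMEC will see by arm. The trial records only serious events, apart from gastrointestinal symptoms, so the way serious events are sorted matters more than it would with full adverse event collection.

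**Working it through.** No arithmetic on trial figures applies. The check sets the stated definition beside the term it defines and follows each kind of event through the text.

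**Is the list closed?** The lead-in says that SUSARs are defined as the development of the items. Nothing marks the items as examples, and no fifth item takes in other events. Local clinicians attribute every SAE, but no sentence lets that judgement move an event into the SUSAR category.

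**Do the items carry causality or expectedness?** Items 2 to 4 carry neither. Item 1 carries a partial product link, because an organism of the product's groups must be isolated, although it need not be a trial strain and the participant need not be in the probiotic arm. For all four, the monitor considers attribution after the event has been called a SUSAR and reported, so attribution is not a condition of entry.

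**Where do the two definitions part?**

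| Kind of event | SUSAR as the article defines it | SUSAR as the term reads | Stated route to the Independent Safety Monitor |
|---|---|---|---|
| A. Listed, judged related and unexpected | yes | yes | immediate |
| B. Multi-organ failure, bowel ischaemia or pancreatitis, judged unrelated | yes | no | immediate |
| C. Unlisted SAE, judged related and unexpected | no | yes | GCP reporting, no time stated; regular review |
| D. Unlisted SAE, judged unrelated | no | no | as for C |

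The definitions disagree in rows B and C.

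**What does the interim SUSAR count contain?** Among these four kinds of event, the article's definition counts A + B and the term's own meaning counts A + C. The difference is (A + B) − (A + C) = B − C. The two totals could therefore agree while being made up of different events. Row C events are not lost to the DMEC, because they remain in the SAE comparison, but nothing there sets them apart as suspected reactions.

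**Can row C occur?** The article allows for reactions in general: Table 1 excludes patients with an earlier adverse reaction to probiotics, and one pilot patient was excluded for that reason (Sample size and recruitment). The article does not say what those reactions were or whether they were serious. Item 1 also needs an isolate, so a serious infection suspected to come from the product but without one is unlisted unless it leads to another listed diagnosis.

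**Was the list arbitrary?** No. The section Testing the hypothesis excludes severe illness, acute pancreatitis and compromised gut blood supply in the light of an earlier trial. The list is a set of foreseen risks, which suits events of special interest but does not define unexpected reactions.

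**The case against.** The strongest reply is that little is lost in practice. Unlisted serious reactions are still SAEs under GCP reporting, local clinicians attribute them, and they enter the interim SAE comparison. Reporting the four diagnoses before attribution is the cautious direction. A randomised comparison of pre-specified diagnoses, whatever their cause, can be interpreted, and the items are printed in the protocol. A condensed article may also leave timelines and the reference for expectedness to the full protocol.

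Most of this stands, and it limits the point in these ways:

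- A reader might infer that an unlisted reaction is not reported immediately. The article does not say so. The timing rests on the cited GCP guidelines, which are not shown. The text supports only that an immediate route to the Independent Safety Monitor is stated for the four diagnoses and for nothing else.
- A reader might infer that most multi-organ failures would be unrelated to the product. The article gives no rate of multi-organ failure. Its 10% allowance for deaths unrelated to diarrhoea concerns loss to follow-up and says nothing about this event or its cause. Patients whose illness requires high dependency or intensive care are excluded at entry.
- Early reporting of unrelated listed events is not itself a defect. The fault is the label they carry and the count they enter.
- It would be wrong to say that all four items ignore suspicion, since item 1 has a product link.
- The entry "SAE = Severe adverse event" under Abbreviations is a clerical slip. The body text uses serious, and the entry adds no weight.

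The objection does not reach the definition itself. That is a rule the article states, not a detail it leaves out, and it conflicts with the term.

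**Conclusion.** The point holds as a wrong stated rule. The SUSAR definition is a closed list of diagnoses, and items 2 to 4 need neither suspected causality nor unexpectedness. An unlisted SAE judged related and unexpected is outside the category, outside its stated immediate route and outside the interim SUSAR count. Multi-organ failure, bowel ischaemia and pancreatitis of any cause are inside all three.

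The size cannot be given, because the article has no rates for any of these events. The effect is confined to safety reporting and to the reading of one interim count; primary outcomes, sample size and efficacy analysis are untouched. The conclusion assumes that the definition is applied as written and that the full protocol does not replace it. If the full protocol defines SUSARs by causality and expectedness, only the article's wording needs correcting. The change is worth making because it is cheap and bears on safety.

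**What to change.** 1. Reconcile the SUSAR definition with the term and with the SAE attribution step in the same section: any SAE assessed as at least possibly related to the investigational product and unexpected is a SUSAR, with the same immediate route to the Independent Safety Monitor that the four diagnoses now have.
2. Keep the four diagnoses and their present immediate reporting, whatever the attribution, under a separate label such as SAEs of special interest.
3. At the interim look at the first 500 participants, tabulate SAEs, special-interest SAEs and SUSARs separately by arm.
4. Correct the SAE entry in the abbreviation list to match the body text.

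The cost is protocol wording, a field on the SAE form for expectedness if it has none, and one extra table. Local clinicians already judge the attribution of every SAE, so no new causality assessment is needed, and no reporting now in place is given up.
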